## Abstract

**Introduction:**

Fifty per cent of patients with cancer require radiotherapy during their disease course, however, only 10%–40% of patients in low-income and middle-income countries (LMICs) have access to it. A shortfall in specialised workforce has been identified as the most significant barrier to expanding radiotherapy capacity. Artificial intelligence (AI)-based software has been developed to automate both the delineation of anatomical target structures and the definition of the position, size and shape of the radiation beams. Proposed advantages include improved treatment accuracy, as well as a reduction in the time (from weeks to minutes) and human resources needed to deliver radiotherapy.

**Methods:**

ARCHERY is a non-randomised prospective study to evaluate the quality and economic impact of AI-based automated radiotherapy treatment planning for cervical, head and neck, and prostate cancers, which are endemic in LMICs, and for which radiotherapy is the primary curative treatment modality. The sample size of 990 patients (330 for each cancer type) has been calculated based on an estimated 95% treatment plan acceptability rate. Time and cost savings will be analysed as secondary outcome measures using the time-driven activity-based costing model. The 48-month study will take place in six public sector cancer hospitals in India (n=2), Jordan (n=1), Malaysia (n=1) and South Africa (n=2) to support implementation of the software in LMICs.

**Ethics and dissemination:**

The study has received ethical approval from University College London (UCL) and each of the six study sites. If the study objectives are met, the AI-based software will be offered as a not-for-profit web service to public sector state hospitals in LMICs to support expansion of high quality radiotherapy capacity, improving access to and affordability of this key modality of cancer cure and control. Public and policy engagement plans will involve patients as key partners.

STRENGTHS AND LIMITATIONS OF THIS STUDYStudy evaluates artificial intelligence (AI) in a broad range of low-income and middle-income countries future roll-out and scale up.Prospective evaluation of all eligible participants per study site to assess factors influencing selection into study.Participating centres need intensity modulated radiotherapy availability with routine use for prostate, cervix and head and neck cancer.Automated contours and plan will be assessed by double-blind peer review according to international quality standards but not directly compared with the manual plan.Comparison of time savings between automated and manual pathways and the budget impact of integrating AI routinely into the clinical workflow.

## Introduction

By 2030, new cancer cases worldwide are projected to rise to 21.3 million annually, of which approximately 70% will be from low-income and middle-income countries (LMICs). Radiotherapy (RT) is a core modality of cancer control and cure for several types of cancer that are common in these settings such as cancers of the cervix, prostate, and head and neck, with 50% of such patients requiring RT during their disease course.^1 2^ However, only 10% of patients in low-income, and 40% of patients in middle-income countries, have access to RT.^3^ Limited resources have contributed to long waiting times for treatment resulting in cancer progression, increased morbidity and inferior survival outcomes, as well as high rates of impoverishing health expenditures.^4^

The WHO has set a target, which states that RT is an essential medical device and should be available to 80% of the world’s population by 2025.^5^ It also recognises that a critical shortfall in the specialised workforce required to deliver RT is the most significant barrier to access.^1^ The Global Taskforce on RT for Cancer Control estimated that by 2035, an additional 30 000 radiation oncologists (RO), 22 000 medical physicists (MPs) and 80 000 treatment radiographers (RTT) would be required to meet demand.^1^

These workforce shortfalls are coupled with a complex RT treatment workflow, requiring several labour-intensive processes from highly trained people including ROs, MPs, dosimetrists (DOs) and RTTs.^6^ The process starts with a dedicated RT CT planning scan, followed by the clinician manually segmenting the (a) tumour (gross tumour volume (GTV)) and (b) areas that are at risk of tumour spread (clinical target volumes (CTVs), eg, regional lymph nodes); organs at risk (OARs) of radiation damage such as the spinal cord, salivary glands, bladder and rectum. This can take 2–3 hours per patient even in the hands of an experienced practitioner. Next, MPs or DOs define the position, size and shape of the radiation beams to ensure adequate coverage of target structures with radiation at the correct dose which can take up to a further half a day.

This pretreatment RT workflow can typically take up to 4 weeks in high-income countries and as long as 12 weeks in LMICs due to patient demand and workforce shortages. In addition, errors and delays can accumulate at each stage of RT planning which can negatively impact the quality of treatment. This includes interclinician variability in target volume delineation which can have a detrimental impact on patient outcomes.^7^

Workforce and skills shortages and lack of financing means countries have been unable to transition from two-dimensional X-ray-based planning to CT-based methods (eg, three-dimensional conformal and intensity modulated RT (IMRT)), which are associated with better outcomes.^8^

The growing demand for RT means that a scalable solution is required to address these challenges. In this regard, a recent WHO report highlighted the potential of digital technologies such as artificial intelligence (AI) to contribute to advancing universal health coverage achieving the Sustainable Development Goals such as ensuring equity in access to treatments and their affordability.^9^

The radiotherapy planning assistant (RPA) is an AI-based software that has been developed to automate two key components of the RT planning pathway:

Contouring of anatomical areas that are at risk of tumour spread (CTVs) and at risk of radiation damage (OARs).Definition of the position, size and shape of the radiation beams to the target organs.

The AI-based contouring models that are included in the RPA were developed by the University of Texas MD Anderson Cancer Centre.^10 11^ User interfaces and AI-based planning for conformal RT treatments were also developed,^12–14^ as were in-built quality assurance tools,^15 16^ and the training and testing of the knowledge-based planning component of the automated planning software which is a function of the Eclipse treatment planning system (Varian Medical Systems). To the best of our knowledge, the RPA is the only application ready for clinical use in head and neck, cervical and prostate cancer which can both contour CTVs and OARs and produce an optimised treatment plan.

The ARCHERY study is a prospective international multicentre study in India, Jordan, Malaysia and South Africa to evaluate the quality, time, resource use and cost associated with using the RPA for the treatment of primary cervical, head and neck, and prostate cancers. The first two cancers represent sites which are leading causes of cancer death in LMICs.^17 18^ In addition, provision of effective, equitable and affordable RT is vital in order to achieve the WHO’s target of eliminating cervical cancer as a public health problem.^19^ Prostate cancer represents a very common cancer where RT plays an important curative role.^17^

We will assess whether the RPA can automate target volume contouring including OARs and produce RT plans that are able to meet international standards for treatment quality. This would also establish whether AI computer-based software can be routinely integrated into the workflow of diverse high volume LMIC centres which vary in their technical and workforce infrastructure to support the AI integration. The study aims to evaluate the extent to which routine use of the RPA will support better workforce allocation and reduce the costs of RT treatment delivery. LMIC centres have been chosen in this evaluation as they have the greatest need at present; however, the study and its goals are also relevant in the HIC setting and therefore the appraisal of the RPA will use current international quality assurance standards rather than direct comparison of outcomes achieved within individual RT centres.^20^

## Methods and analysis

### Patient inclusion criteria

Patients with:Histologically confirmed head and neck cancers of the oropharynx, larynx, hypopharynx and nasopharynx (American Joint Committee on Cancer (AJCC) stages I–IVB) that has given consent for radical RT. Induction chemotherapy prior to RT acceptable.ORHistologically confirmed primary cervical cancer (International Federation of Gynaecology and Obstetrics/AJCC stages IB–IIIC1) that have given consent for radical RT. Induction chemotherapy prior to RT or concurrent chemoradiotherapy acceptable.ORHistologically confirmed primary prostate cancer (AJCC stages I–IIIC) that have given consent for radical RT.Provide signed informed consent to participate in the study.Aged ≥18 years.

### Patient exclusion criteria

Patients requiring RT after curative surgery or surgery that is intended to remove as much of the tumour as possible.Patients receiving palliative RT.

Consecutive patients who are eligible will be approached and screening data collected to establish the proportion of eligible patients that consent to participate. Participants are only eligible for the study if they have already provided consent to receive radical RT and participation in ARCHERY will not change how the patient is treated.

### Site exclusion criteria

Centre using exclusively cobalt-based RT for treatment.Centres not using standardised international guidelines/protocols for target volume contouring and dosimetric radiation constraints.

### Study conduct

The AI-based RT planning tool (the RPA) will be applied to the CT scan acquired as part of a participants planned RT treatment process.

The RPA will be used to automate:

CTV and OAR contouring.Treatment planning.

Randomisation is not required as the initial CT scan of the participant, which is used as the template for contouring and planning, will be used for both the standard and automated approaches. Patients will be treated on the standard plan and will not be affected by the study. Local centres will remain blinded to the results of the automated plans.

### CTVs and OAR contouring

Contours will be applied manually to the primary tumour GTV (eg, for head and neck) by the treating clinician.

This CT scan with the contoured GTV will be used for the manual and the automated study pathway (figure 1) to create plans 1 and 2. The contouring of CTVs and OARs will be performed by the clinician (blue boxes in figure 1) or the automated by AI using the RPA (orange boxes in figure 1).

**Figure 1 F1:**
[figure not shown]
Study workflow. CTV, clinical target volume; GTV, gross tumour volume; OAR, organs at risk; RTTQA, RT Trials Quality Assurance.

For the prostate cancer pathway, there will be no GTV to be outlined but a CTV (prostate gland±seminal vesicles) as per current international guidance which will be outlined by the clinician or the RPA.

### Treatment planning

Two plans will be produced for evaluation. Plan 1: Manual contours will undergo planning using standard clinical protocols by a DO or physicist at the local site, and this will be used to treat the patient (blue box in figure 1). Plan 2: The automated contours will undergo autoplanning and this will undergo clinical evaluation (orange box in figure 1).

### Quality assessment protocol

The final RT plans will be exported as DICOM (Digital Imaging and Communication in Medicine) files, to the UK RT Trials Quality Assurance (RTTQA) group who will coordinate the assessment of contouring (CTVs and OARs) and planning (dose distribution) produced by the RPA. An international panel all with greater than 10 years of experience as an RO will undertake the evaluation of the treatment contours using a protocol based on international standards for target volume definition and dosimetry.

### Procedures for assessing efficacy

The primary outcome measure is overall treatment plan acceptability, a composite outcome including both the assessment of the delineated CTVs and OARs with reference to internationally accepted contouring guidelines and the adherence to predefined dosimetric constraints (table 1). We will not collect patient outcomes following treatment as important clinical differences in terms of toxicity and tumour control are not expected if these validated criteria are met and patients will not be treated on the automated plans. In addition, variation in the accuracy of patients set up across the centres for treatment may result in important differences in patient outcomes unrelated to the quality of the manual or automated contours.^21 22^

**Table 1 T1:** Assessment procedures for each treatment plan based on a composite score

Contouring	Dosimetry	Overall assessment
Score 3 or 4	Score 3 or 4	Acceptable
Score 3 or 4	Score 1 or 2	Unacceptable
Score 1 or 2	Score 3 or 4	Unacceptable
Score 1 or 2	Score 1 or 2	Unacceptable

The automated plan (plan 2) will be analysed against the expected plan acceptability rate from the literature which estimates that 95% of RT plans will be acceptable (scores 3 and 4 according to study scoring criteria) for treatment without the requirement for major edits (scores of 1 or 2).^7 23^ Major edits (as defined using the Global Quality Assurance of Radiation Therapy Clinical Trials criteria) are edits that if not undertaken would affect the likelihood of cure, locoregional control and could result in additional toxicity.^24^

The assessment of the contours and dosimetry from the automated plans will be coordinated by the RTTQA group and use international standards and procedures for RT planning quality assurance which have been agreed by the Global Quality Assurance of Radiation Therapy Clinical Trials Harmonisation Group (GHG) https://rtqaharmonization.org.

The RTTQA group will develop procedures and guidelines for OAR and CTV contour assessment in line with international standards for normal tissue and nodal CTVs for cervical, head and neck and prostate cancer^25–30^ that will be used by the peer reviewers in their assessments.

A scoring framework developed with reference to GHG protocol variation definitions will be provided for assessment of contouring with examples given of contours considered clinically not acceptable. The Likert scale below (with potential scope for minor changes) will be used for the grading of contouring:

Score 4—Acceptable—per protocol: No edits required. The current contours are clinically acceptable and could be used for treatment without change.Score 3—Acceptable variation: Minor edits, not expected to have a major clinical impact on treatment outcome. Edits to the current contours should be considered.Score 2—Unacceptable variation: Major edits, may affect the likelihood of cure, locoregional control and potentially cause additional toxicity. The current contours are clinically unacceptable.Score 1—Unacceptable variation with treatment modification: Major edits, however, these variations could not have been reasonably avoided due to clinical necessity as perceived by the treating physician.

Two reviewers will independently review each set of contours. If there is any discordance between the two reviewers, that is, an unacceptable score (1 or 2) by one reviewer and acceptable score (3 or 4) by another, a third reviewer will be consulted, and acceptability will be defined based on a consensus majority rule (2:1).

The dosimetric assessment of the plans will be automated using the autoextracted dose volume histogram (DVH) constraints. The framework for assessment will be defined for each tumour cohort with reference to GHG criteria.^31^ If any of the DVH constraints are not met, the plan would be assessed independently by two peer reviewers to evaluate whether there is any mitigation for the dosimetric constraints not being met (eg, extensive tumour), otherwise the plan will be graded as clinically unacceptable.

Dosimetric constraints will be based on contemporary RT IMRT RCT protocols for cervical, head and neck, and prostate cancer^27 32 33^ but will also require an understanding of differences in protocols used across different regions. The Likert scale below will be used for grading of DVHs:

Score 4—Acceptable—per protocol: The radiation therapy treatment was planned according to protocol specifications. Mandatory and optimal volume planning constraints are met.Score 3—Acceptable variation: The radiation therapy treatment was not planned according to all the protocol specifications, but not expected to have a major clinical impact on treatment outcome. Mandatory volume planning constraints are met but not all the optimal volume planning constraints are achieved.Score 2—Unacceptable variation: The radiation therapy treatment was not planned according to protocol specifications and may affect the likelihood of cure, locoregional control and potentially cause additional toxicity.Score 1—Unacceptable variation with treatment modification: The radiation therapy treatment was not planned according to protocol specifications and may affect the likelihood of cure, locoregional control and potentially cause additional toxicity. However, these variations could not have been reasonably avoided due to clinical necessity as perceived by the treating physician.

### Quantifying and modelling the time cost savings from using the RPA by using the ESTRO approved time-driven activity-based costing model

To determine the time savings from the automated approaches compared with the manual approach, time-and-motion studies will be undertaken to populate the ESTRO time-driven activity-based costing model.^6^ This is considered the most contemporary and robust mechanism for radiation therapy costing and will be used to estimate the cost of delivering RT treatment for each tumour type in each centre, in addition to computing the actual personnel and equipment resource utilisation.^6^

The model requires time estimates for all RT processes within the typical RT care pathway including time for contouring anatomy including edits, plan production, peer review, QA checks, plan acceptance and treatment delivery.^34^ All times will be stratified according to the specialist personnel involved and undertaken for each of the two study planning pathways outlined in figure 1, that is, the (1) standard manual pathway and (2) fully automated pathway.

Allied to this will be the collection of detailed information at the centre level of the available resources and their associated costs. This includes:

Indirect resources: resources (and their costs) that cannot be directly assigned to a single treatment, that is, personnel, equipment and related infrastructure and maintenance including overheads.Direct material costs related to a particular treatment course (masks, fiducials, contrast material).Information on the number of RT courses delivered in the centre (by tumour type, treatment intent, fractionation, complexity).

The outputs from the workflow timings study and data collection on the resources available and courses delivered at each individual centre will be key inputs into the model to estimate differences in costs and resource needs for cervical cancer, head and neck cancer and prostate cancer treatment courses using the two approaches (fully automated vs standard).

Using this information, we will be able to assess the impact on resource needs and associated costs (in particular for specialist personnel, eg, ROs from scaling up automation to other cancer types, and undertake cost-minimisation and budget impact analyses).^35^ The costing and cost-saving calculations will be performed at the level of each country and centre. The budget impact analysis will inform the affordability of the intervention to the health system, in terms of the feasibility of expanding the number of patients that can be treated with RT.^36^

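### The cost-minimisation analysis assumes that automated and manual plans are of equal quality, which the design does not test, and no rework cost is tied to the observed share of unacceptable automated plans.

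*Protocol article*

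**What the plan says.** The costing section of the protocol article (time-driven activity-based costing) plans to "undertake cost-minimisation and budget impact analyses", with calculations by country and by centre. The results are to inform affordability and how far the number of patients treated could grow. The model takes times for contouring and its edits, plan production, peer review, quality checks, plan acceptance and treatment delivery, for the manual and the fully automated pathway.

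On quality, only one of the two plans is assessed:
- Treatment planning: "Plan 2: The automated contours will undergo autoplanning and this will undergo clinical evaluation". Plan 1, the manual plan, is the one used for treatment.
- Quality assessment protocol: the files go to the quality assurance group, "who will coordinate the assessment of contouring (CTVs and OARs) and planning (dose distribution) produced by the RPA".
- Strengths and limitations list after the abstract: the automated output is "assessed by double-blind peer review according to international quality standards but not directly compared with the manual plan".
- Introduction: the appraisal "will use current international quality assurance standards rather than direct comparison of outcomes achieved within individual RT centres".
- Procedures for assessing efficacy: "The automated plan (plan 2) will be analysed against the expected plan acceptability rate from the literature", put at 95%. The same section expects no important clinical difference provided the acceptability criteria are met.

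Study conduct adds that centres are blinded to the automated results.

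**The concern.** Cost-minimisation compares costs alone, so it is interpretable only if the two options give the same outcome. Here the manual plans are never scored, and equality with them rests on an external rate and an expectation. That expectation is itself conditional: it covers plans that meet the criteria. Plans scored 1 or 2 do not meet them, and score 2 is defined as variation that may harm tumour control or add toxicity. For the automated pathway as a whole, equal outcome would therefore require failed plans to be corrected, and correction takes staff time.

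The article does not say how the observed share of failed plans enters the automated pathway's cost. Because patients are treated on plan 1 and centres do not see the results for plan 2, it describes no correction of a rejected automated plan that a time-and-motion study could record. Manual edits do occur in routine care and can be timed. At stake are the size of the reported saving and the budget-impact figures built on it, most of all in centres where automation fails more often than average.

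**Working it through.** **1. The plan's own figure.** Inputs from the Sample size section: expected acceptability p1 = 0.95, limit p0 = 0.90, one-sided alpha 0.025, power at least 90%, about 330 per tumour type.

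Normal approximation: n = (1.960·√(0.90·0.10) + 1.2816·√(0.95·0.05))² / 0.05² = 300.9, so 301. With continuity correction, (n/4)·(1 + √(1 + 2/(n·0.05)))² = 320.6, so 321, within 3% of 330. The exact binomial test at n = 330 has power 93.0%. The stated 330 is consistent with its inputs.

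**2. How many failures a successful cohort allows.** The smallest number acceptable, x, with P(X ≥ x | 330, 0.90) ≤ 0.025 is 308 (attained alpha 0.0224).

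| Acceptable | Exact 95% interval | Meets criterion |
|---|---|---|
| 307/330 | 89.7% to 95.5% | no |
| 308/330 | 90.1% to 95.8% | yes |

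Up to 330 − 308 = 22 plans may be unacceptable: 22/330 = 6.7%. Success therefore does not show a rate of 95%, nor equality with manual plans. This rule ignores the centre adjustment and cluster-robust errors of the planned analysis, so 22 is approximate.

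**3. Staff time if failed plans are fully redone by hand.** The Introduction gives 2 to 3 hours for contouring and up to half a day for planning. Taking half a day as 240 minutes (assumption), the manual total is 360 to 420 minutes.
- 5% failure: 0.05 × 360 = 18 to 0.05 × 420 = 21 minutes per patient.
- 6.7% failure: (22/330) × 360 = 24 to (22/330) × 420 = 28 minutes per patient.

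These are upper figures for those failure rates. The 2 to 3 hours include gross tumour volume contouring, which is manual in both pathways where it applies, and a dosimetry-only failure need not mean recontouring.

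**4. Effect on the saving.** Set manual cost to 1, automated cost to a, and the unacceptable shares to u_A (automated) and u_M (manual), each failure costing one full manual replan. Then

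saving = (1 + u_M) − (a + u_A) = (1 − a) − (u_A − u_M).

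| u_A | u_M | Change in saving, points of manual cost |
|---|---|---|
| 5% | 0 | −5.0 |
| 6.7% | 0 | −6.7 |
| 10% | 0 | −10.0 |
| 5% | 5% | 0 |
| 6.7% | 5% | −1.7 |

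The documents give no unit costs, so a is unknown. With u_M = 0 and a = 0.10, the saving falls from 0.90 to 0.85 (5%) or 0.83 (6.7%). With a = 0.50, it falls from 0.50 to 0.45 or 0.43. It vanishes only when a + u_A reaches 1, that is, when automated cost is already about 93% to 95% of manual cost at these failure rates.

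**The case against.** The lack of a manual comparator is disclosed and reasoned. The article lists it as a limitation, explains that international standards replace comparison with individual centres, and ties the expectation of similar outcomes to explicit criteria. That is a defensible choice for the primary outcome. It does not supply the equality that cost-minimisation needs.

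A reader might infer that rejected automated plans are costed as if they needed no rework. The article does not say so. Edits, plan production and plan acceptance are timed in both pathways, so some rework may already be counted, and a full protocol or health-economic plan may say more. What stands is narrower: no stated link between the observed unacceptable share and a cost, and no described step at which the rework is observed.

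A reader might also infer that the cost conclusion is unsupported altogether. That goes too far. Time savings and budget impact do not depend on equal quality in the way cost-minimisation does, and the cost-minimisation result is conditional rather than void.

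Charging rework to the automated side alone would be one-sided, because the article's 95% refers to radiotherapy plans in general. This objection stands and shapes the size given in the verdict. It also stands that score 1 denotes variation judged unavoidable, so manual replanning may not remove it.

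**Conclusion.** The point holds in limited form. Cost-minimisation rests on an assumption of equal quality with local manual plans that the study does not test, and meeting the primary criterion would not establish it. The failure share is not connected to a rework cost in the article.

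The effect is at most about 5 to 7 points of manual contouring and planning time if manual rework is zero and 5% to 6.7% of automated plans fail. It is nil if both pathways fail at 5%, and about 1.7 points at 22/330 against 5%. Centres with higher automated failure would see more, for example 10 points at 10% with no manual rework. The direction of the saving is unlikely to change. These figures assume independent plans, half a day taken as 240 minutes, and full manual redoing of every failed plan. The difference in quality between the pathways is unknown in either direction.

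**What to change.** 1. Replace cost-minimisation with a cost-consequence presentation: cost and staff time shown alongside acceptability, or per acceptable plan. State that equality with local manual plans is assumed.
2. In the costing and budget-impact models, add a rework cost for unacceptable automated plans at the observed failure rate by centre and tumour type, with its uncertainty. Separate contour failures (recontour and replan) from dosimetry-only failures (replan), and exclude manual gross tumour volume time common to both pathways. Show score 1 plans with and without this charge.
3. Treat the manual pathway the same way in a sensitivity analysis, with 95% acceptable as base case and a range labelled as an assumption.

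Running the automated dose-volume check on plan 1 would not test equal quality. Each plan would be judged on its own contours, and contour quality would be left out.

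The cost is slightly more modelling work, using scores and times already being collected, and possibly a smaller reported saving. Recruitment and treatment are unaffected.
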